#### Secondary outcomes

##### Endoscopic and histopathological examination

The change in red plaques, hemorrhagic spots/plaques, erosion and bile reflux at endoscopy and the grade of active chronic inflammation and chronic inflammation in the gastric mucosa, depending on the histopathological examination of biopsy specimens, will be compared between visits one and six, according to the consensus on CG in China.

##### Eradication rate of Helicobacter pylori

The eradication rate of HP after treatment will be used to evaluate the effects of JWQTP.

##### The treatment efficacy in the Chinese medicine field

To evaluate the therapeutic effect in the CM field, the TCM symptom score system (Table 3) will be used, following the *Guidelines for Clinical Research on Chinese New Herbal Medicines* (*Trial Implementation*). In the symptom score system, the score of the primary symptom will be based on the severity, duration and frequency of the symptoms. Secondary symptoms will be scored by grading. The final point will be determined by the sum of all symptom scores. The CM therapeutic effect Index (CMTEI), as calculated with the following formula, will be used to evaluate treatment efficacy in the CM field.

**Table 3 T3:** **The traditional Chinese medicine (TCM) symptom score system for chronic non-atrophic gastritis (CNG**)

**Symptom**			**Score**	**Grading system**
**Primary symptom**	Epigastric pain	Degree		0 score: None
				2 score: Mild pain, does not affect work and life, VAS score 1 to 3
				4 score: Moderate pain, affects work and life partly, VAS score 4 to 6
				6 score: Severe pain, affects work and life fully, need rest, VAS score 7 to 10
		Duration		0 score: None
				2 score: Less than 1 hour a day
				4 score: 1 to 2 hours a day
				6 score: More than 2 hours a day
**Total primary symptom scores**				Degree score + Duration score
**Frequency of epigastric pain**				Score = the days of pain attack in a week (for example, a score of 7 indicates pain everyday)
**Secondary symptoms**	Weakness and lassitude			0 score: No
				2 score: Yes
	Dry mouth/bitter taste in mouth			0 score: No
				2 score: Yes
	Loss of appetite			0 score: None
				1 score: food intake reduced by 1/3
				2 score: food intake reduced by 1/3 to 2/3
				3 score: food intake reduced by 2/3
	Distention and fullness			0 score: None
				1 score: Mild,
				2 score: Moderate, does not affect work and life
				3 score: Severe, need drug control
	Loose stool			0 score: No
				2 score: Yes
	Belching			0 score: No
				2 score: Yes
**Total symptom score**				Total symptom score = total primary symptom scores + total secondary symptom scores. Frequency of epigastric pain score is calculated independently.

$$\begin{array}{l} \mathrm{CMTEI}=\\ \left(\frac{\mathrm{symptom}\;\mathrm{score}\;\mathrm{before}\;\mathrm{treatment}‒\mathrm{symptom}\;\mathrm{score}\;\mathrm{after}\;\mathrm{treatment}}{{}_{*100\%}\;\mathrm{symptom}\;\mathrm{score}\;\mathrm{before}\;\mathrm{treatment}}\right) \end{array}$$

The classification of treatment efficacy is shown as follows: CMTEI ≥95% indicates clinical recovery; 95% > CMTEI ≥70% indicates remarkable recovery; 70% > CMTEI ≥30% indicates modest recovery; and CMTEI < 30% indicates inefficiency.

#### The change in the patient-reported outcome instrument for chronic gastrointestinal diseases

Although the symptoms of chronic gastritis are not specific, the relief of clinical symptoms remains a major therapeutic aim. The patient-reported outcome (PRO) instrument for chronic gastrointestinal diseases (http://www.proqolid.org/) [20], a 6-dimension, 35-item instrument, will be performed on visits one and six, and the results will be used to compare the two visits to assess any changes in quality of life. The 35 items of the instrument are the following: fatigue, disturbed sleep, no hunger sensation, decreased appetite, afraid of society, dry mouth or bitter taste in mouth, bad breath, pharyngeal foreign body sensation, acid regurgitation, hiccup or belching, nausea or vomiting, burning pain behind the sternum, retrosternal pain, stomachache, gastric distension, gastric discomfort, stomach burning, abdominal pain, abdominal distension, degree of retrosternal pain, degree of heartburn, degree of stomachache, degree of gastric distension, degree of abdominal pain, degree of abdominal distension, diarrhea, constipation, incomplete sensation after defecation, defecation urgency, weight loss, emotional fluctuation, anxiety or nervous, worry about disease, impact on social activities and impact on family status and function. All of the items fall into five levels, which are scored as 0, 1, 2, 3 or 4, except for decreased appetite, which is grouped into four levels and scored as 0, 1, 2 or 3. The final score will be determined by the sum of all symptom scores.

#### Safety outcomes

We will perform the following tests on all subjects to screen for the JWQTP administration during the study: physical examination (temperature, respiration, heart rate, blood pressure, height and weight), complete blood cell count, urinalysis, stool examination, fecal occult blood test, liver function (ALT, AST, alkaline phosphatase (ALP), serum total bilirubin (STB), and γ-glutamyl transpeptidase (γ-GT)), renal function (Cr, micro albuminuria, serum cystatin C, and urine N-acetyl-β-glucosaminidase) and electrocardiogram (ECG) at the first, fourth and sixth visits. In addition, a urine pregnancy test will be carried out for female patients of childbearing age (Figure 2).

#### Data management

The completed CRFs will be submitted to the statistical department after the inspections of the clinical investigators and trial inspectors for data entry and management. All data will be entered twice electronically using the EpiData3.1 database by two independent data managers to ensure data accuracy. The investigators will resolve any problems encountered by the data managers’ concerning the data as soon as possible. Then, the data managers will make corrections to the data, according to the investigators’ instructions. A blind review will be performed among the data managers, predominant investigator and sponsor to compile a report about the quality of data management. The database will be locked by the statistician, predominant investigator and sponsor after the blind review and confirmation of database accuracy. Then, the final trial dataset will be disclosed by an independent assistant according to the randomization list, where the data will be grouped into groups A, B or C, and an independent statistician will make statistical analysis using SAS 9.2 in a semi-blinded manner with no suggestion of the exact treatment allocation. Finally, the predominant investigator will write a conclusive report of the statistical analysis in an unblinded manner. Because there will be unified training prior to the study, regular supervisor’s visits, data review by the clinical investigators, revisions by the data managers and a blind review for the data after the study, no further data management committee will be set up to ensure the data’s accuracy and validity. Only the clinical investigators and trial inspector will have access to the medical records of the subjects, and they will all sign a confidentiality agreement. Anonymous data will be used for the inspection of the pharmaceutical supervisory and administrative department. Subjects’ medical records will be stored in the data archive of the drug clinical trial agency after analysis.

#### Adverse event reporting

The safety of subjects is of paramount importance during the study period, and every adverse event should be documented on the adverse event form (AEF) in great detail. Adverse events (AEs) include any new diseases and exacerbations of CNG or comorbidities related or unrelated to the treatment. Any fatal, life-threatening, disabling or event severe enough to warrant hospital admission or prolonged hospital stays occurring after any dose of treatment pill and at any time during this study should be considered an SAE. All of these data should be recorded on an AEF with the corresponding treatment and reported to the China Food and Drug Administration (CFDA), provincial-level Food and Drug Administration, sponsor and Independent Ethics Committee within 24 hours. Then, the sponsor will inform the other four sites as soon as possible. The severity of an AE is classified into three degrees: mild, moderate and severe. For the mild degree, a small amount of indisposition arises, which the subject can bear without any intervention and without influencing the trial. For the moderate degree, a moderate amount of indisposition develops, and some intervention should be taken to get the trial going. For the severe degree, an enormous amount of indisposition dictates that the subject should quit the trial for his or her own safety. In the case of an SAE, the investigator can break the blind to discover the subject’s treatment allocation by reading the emergency letter corresponding to the group allocation. Any AE related to the test drug will be treated for free. On a separate note, any subject with an intervention for AE must undertake a follow-up visit within half a month for his or her health.

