### Withdrawal criteria

Withdrawal criteria include:

1. Intolerance to worsening conditions.

2. Quitting voluntarily.

3. Having manifestations of hemorrhage of the digestive tract, such as melena or hematemesis during the study.

4. Experiencing anaphylaxis following the trial drug’s administration.

5. Adverse medical events occurring during the study, such as severe liver function damage, malignant tumors in other system, and accidental pregnancy or other reasons, as judged by the investigators, that might make the patient unlikely to complete the study.

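### The AE severity scale has no valid grade for symptom-free laboratory and ECG abnormalities, and it mixes severity with the decision to leave the trial

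*Protocol article*

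**What the plan says.** The section Adverse event reporting prints a complete three-level severity scale:

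- Mild: "For the mild degree, a small amount of indisposition arises, which the subject can bear without any intervention and without influencing the trial".
- Moderate: "For the moderate degree, a moderate amount of indisposition develops, and some intervention should be taken to get the trial going".
- Severe: "For the severe degree, an enormous amount of indisposition dictates that the subject should quit the trial for his or her own safety".

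The same section defines what counts as an event: "Adverse events (AEs) include any new diseases and exacerbations of CNG or comorbidities related or unrelated to the treatment". Seriousness is defined separately, by outcome: "Any fatal, life-threatening, disabling or event severe enough to warrant hospital admission or prolonged hospital stays".

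The section Safety outcomes plans blood count, urine and stool tests, five liver tests (ALT, AST, ALP, total bilirubin, γ-GT) and "renal function (Cr, micro albuminuria, serum cystatin C, and urine N-acetyl-β-glucosaminidase) and electrocardiogram (ECG) at the first, fourth and sixth visits".

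Withdrawal criteria, item 5, gives "severe liver function damage" as an example of an adverse event that can lead to withdrawal. It sets no limit and does not refer to the severity scale.

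Statistical analysis plans a chi-square or Fisher test of AE incidence between groups, a descriptive listing of AEs, and a separate analysis that involves drop-out due to AEs. It names no analysis by severity grade.

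**The concern.** A severity grade should say how bad an event is. This scale asks three things at once: how unwell the subject feels, whether anything was done, and whether the subject can continue. Two problems follow.

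First, most of the planned safety outcomes are measurements that can be abnormal without the subject feeling anything. A scale on which every grade starts from indisposition has nothing to hold on to for such findings. Investigators at five sites would each have to improvise, and a large untreated rise could be entered at the same grade as a trivial one.

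Second, severity and disposition are partly the same information. Severe is worded as a reason to leave, and moderate as something managed so that the subject can go on. A count of severe events then tells the reader less than it should beyond the AE drop-out figure.

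Safety and any dose-effect relationship are stated objectives, and the results are meant to support a phase III programme. A severity column that cannot place organ-function findings weakens the comparison of high dose, low dose and placebo.

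**Working it through.** No figure in the plan depends on this point, so there is nothing to recompute. The check applies the printed definitions to the events that the protocol plans to look for.

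**Step 1. Elements of each grade**

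| Grade | Indisposition | Intervention | Participation |
|---|---|---|---|
| Mild | small, bearable | none | not affected |
| Moderate | moderate | some | kept going |
| Severe | enormous | not stated | subject should quit |

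**Step 2. A symptom-free liver, renal or ECG abnormality of any size (indisposition: none)**

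| Case | Mild | Moderate | Severe | Result |
|---|---|---|---|---|
| (a) no intervention, subject continues | meets two of three elements; fails only because no indisposition arises | fails on indisposition and intervention | fails on indisposition and participation | nearest to mild, whatever the size |
| (b) intervention, subject continues | fails on intervention | fails on indisposition | fails on indisposition and participation | no grade fits |
| (c) subject leaves the trial | fails on participation | fails on indisposition and participation | fails on indisposition | no grade fits |

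The size of the abnormality enters none of the cells. Strictly, even case (a) is outside the scale, because mild still supposes that some indisposition is felt.

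**Step 3. Can such findings be AEs at all?** The AE definition speaks of new diseases and exacerbations and does not name laboratory or ECG findings. Withdrawal criteria, however, lists serious liver impairment among adverse medical events, so at least some organ-function findings are meant to be AEs and need a grade.

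**Step 4. Severity against drop-out.** Severe requires both enormous indisposition and a judgement that the subject should quit. Any event correctly graded severe is therefore one that should end participation, which places it in the AE drop-out category if the judgement is followed. The reverse does not hold: case (c) is an AE drop-out that is not severe on this scale, and subjects may also leave voluntarily, through accidental pregnancy, or for using forbidden drugs. The two overlap by definition but are not identical.

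**Step 5. What uses the grade?**

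- SAE status rests on outcome, not on the grade.
- The 24-hour reporting and the SAE provision for breaking the blind follow SAE status.
- The safety criterion for suspending or terminating the study refers to SAEs caused by the trial drugs.
- The named AE test is on incidence.
- The laboratory and ECG values are collected at visits 1, 4 and 6 regardless of the grade.

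What remains is the severity entered on the AE form and any listing or description built on it.

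**The case against.** The other side can fairly say the following.

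- **Silent abnormalities do not all become mild.** This is correct. A reader might infer that the scale systematically down-grades them, but mild excludes events that need intervention or affect participation. For those events the fault is that no grade fits.
- **Severe is not another name for discontinuation.** This is also correct. It requires enormous indisposition, speaks of what the subject should do, and many withdrawals are not severe AEs. The mild/moderate split also carries information among subjects who stay. Only the overlap stands.
- **The withdrawal criterion does not contradict the scale.** A reader might see a conflict between "severe liver function damage" and a scale that cannot call a symptom-free liver finding severe. The criterion uses ordinary language, leaves the judgement to the investigator and works whatever grade is entered. The two uses of the word need aligning, but this is not a direct contradiction.
- **The entry limit proves nothing.** Exclusion criterion 4 uses 1.5 times the upper limit of normal for ALT and AST. That limit decides eligibility and need not define on-treatment severity.
- **Laboratory grading bands may sit in the full protocol or AE form.** Their absence from an article would not be a finding. Here, however, the article prints the scale itself, and as printed it ties every grade to indisposition. That can be judged as written.
- **Little depends on the grade.** This stands, and it limits the importance of the point.

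**Conclusion.** The point holds in limited form. The scale has no valid grade for symptom-free laboratory and ECG abnormalities: untreated, they fall nearest to mild at any size; treated or leading to withdrawal, they fit nowhere. It also mixes severity with the decision to leave, so severe overlaps by definition with AE drop-out.

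The harm is to severity as recorded and listed by arm. A reader might infer that organ toxicity would be hidden from the phase III decision. The document does not support that, because the values are safety outcomes in their own right and SAE handling and the AE incidence test do not use the grade.

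The document gives no incidence of such abnormalities, so the number of affected events cannot be estimated. The conclusion assumes that the printed definitions are those on the AE form, that at least some laboratory or ECG abnormalities are recorded as AEs, and that severity appears in the AE listing. Importance: minor to moderate.

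**What to change.** 1. Grade laboratory and ECG abnormalities by size, independent of symptoms, on a scale that the investigators fix before recruitment. No clinical limit is proposed here.
2. Grade symptomatic events by intensity and effect on daily function.
3. Remove intervention and trial continuation from the grade, and record them in a separate action-taken field on the AE form.
4. Reconcile the sections Withdrawal criteria, Safety outcomes and Adverse event reporting, so that severe has one stated meaning or the different uses are distinguished.

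The cost is rewording the AE form and adding the scale to the investigator training already planned. The values are collected anyway, and Trial status says that recruitment was still being prepared when the article was submitted. The downside is that some events now called mild will be reported at a higher grade.

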### Concomitant treatments and forbidden drugs

Subjects will be permitted to continue concomitant treatment for comorbidities, such as hypertension, chronic bronchitis, stroke or skin disease, which will not affect the trial’s final results. However, they are forbidden to take any CM or Western medicine related to CNG, such as prokinetics, cholinergic agents, H2-receptor antagonists, proton pump inhibitors, mucosal-protective agents or antibiotics for the eradication of HP. Aspirin, nonsteroidal anti-inflammatory drugs, sedative hypnotics, antidepressants and opioids should be used sparingly. Each concomitant treatment should be documented strictly in the CRF, and once a subject is found to be taking forbidden drugs, he/she will be withdrawn from this study.

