### Outcome measurement

#### Primary outcome

The eradication of epigastric pain is considered the primary outcome to evaluate therapeutic effects. The visual analogue scale (VAS) score (0 to 10 numeric pain intensity scale) for epigastric pain was measured at every visit, ranging from 0 to 10, where a score of 0 suggests no epigastric pain and a score of 10 indicates the most severe epigastric pain. The eradication of epigastric pain is defined as a score of VAS that stops rising after dropping to 0 during the study. The eradication rate of epigastric pain will be compared among the three groups, together with the change in VAS scores before and after treatment in each group.

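### The rules for a moderate CNG exacerbation treated with a CNG medicine are not reconciled, and the primary endpoint can count pain relief on that medicine as a success of the assigned arm

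*Protocol article*

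**What the plan says.** All places are in the protocol article.

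- **Adverse event reporting.** "Adverse events (AEs) include any new diseases and exacerbations of CNG or comorbidities related or unrelated to the treatment". Every event is then graded. A mild event is one "which the subject can bear without any intervention and without influencing the trial". For a moderate event, "some intervention should be taken to get the trial going". For a severe event, "an enormous amount of indisposition dictates that the subject should quit the trial for his or her own safety". The kind of intervention is not named.
- **Concomitant treatments and forbidden drugs.** Subjects may continue treatment for comorbidities, but "they are forbidden to take any CM or Western medicine related to CNG". The consequence is that "once a subject is found to be taking forbidden drugs, he/she will be withdrawn from this study". There is no exception for a medicine given to treat an adverse event.
- **Withdrawal criteria, item 1.** A patient who cannot tolerate worsening is withdrawn.
- **Primary outcome.** Eradication is "a score of VAS that stops rising after dropping to 0 during the study". Other CNG medicine is not mentioned.
- **Statistical analysis.** The full analysis set (FAS) is primary. Missing values are filled by last observation carried forward (LOCF), so that the analysed population matches the starting one. FAS patients who leave are evaluated at the time of withdrawal.

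**The concern.** Take a patient with a moderate exacerbation who is given a CNG-related medicine. The adverse event section points towards intervening and continuing, and the forbidden-drug section requires withdrawal. Neither mentions the other, nor the withdrawal criterion on worsening.

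The case is foreseeable. Epigastric pain is required for the syndrome diagnosis, a third of patients take placebo for 8 weeks, and most drug classes that the Background and Discussion name for CNG are among the forbidden examples.

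The statistical stake is the binary primary endpoint. As defined, it credits the assigned arm with a pain score of 0 that may have been reached on another CNG drug. If JWQTP works, treated exacerbations should be commoner on placebo. The placebo rate would then rise more than the active rates, and the observed difference would be too small.

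**Working it through.** **1. Scoring under the stated rules.** Apply the primary definition, LOCF and evaluation at withdrawal to a patient who takes a CNG-related medicine for an exacerbation:

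| Course | Value used | Primary score |
|---|---|---|
| Stays in; VAS falls to 0 on the medicine and does not rise | 0 | Eradicated |
| Withdrawn at a visit where VAS is 0 on the medicine | 0 carried forward | Eradicated |
| Withdrawn at a visit where VAS is above 0 | above 0 carried forward | Not eradicated |
| Withdrawn for a non-pain exacerbation, last VAS already 0 | 0 carried forward | Eradicated |

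Rows 1 and 3 can be the same patient handled differently. Row 2 shows that strict withdrawal alone does not remove the problem.

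**2. The plan's own sample size.** Inputs from Sample size calculation: 55% v 30%, α = 0.05, power 0.85. Two-sided testing is from Statistical analysis. With unpooled variance:

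n = (1.960 + 1.036)² × (0.55×0.45 + 0.30×0.70) / 0.25² = 65.7, so 66 per group, as stated.

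**3. Base for the FAS.** LOCF keeps everyone, so n is 240/3 = 80 per arm. For one JWQTP arm against placebo:

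power = Φ( (pA − pP) / √{[pA(1−pA) + pP(1−pP)]/n} − 1.960 )

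At 55% v 30% and n = 80: SE = √(0.4575/80) = 0.0756; 0.25/0.0756 = 3.306; Φ(1.346) = 0.911. At n = 66 the result is 0.851.

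**4. Illustration.** Assumptions, none from the documents:

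- 55% and 30% are the eradication rates when every treated exacerbation counts as a failure.
- A share e of each arm is treated with a CNG medicine.
- A fraction r of those treated reach VAS 0 and count as eradicated.

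Each rate becomes p + e·r. In the first row, for example, active is 0.55 + 0.05×0.5 = 0.575 and placebo is 0.30 + 0.10×0.5 = 0.35.

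| e placebo / active | r | Active v placebo | Power, n = 80 | Power, n = 66 |
|---|---|---|---|---|
| 10% / 5% | 50% | 57.5% v 35% | 0.834 | 0.758 |
| 10% / 5% | 80% | 59% v 38% | 0.776 | 0.695 |
| 20% / 10% | 50% | 60% v 40% | 0.733 | 0.650 |
| 20% / 10% | 80% | 63% v 46% | 0.59 | 0.51 |
| 5% / 5% | 50% | 57.5% v 32.5% | 0.907 | 0.847 |

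The fourth row is the extreme corner. The last row shows that the loss comes almost wholly from unequal treatment between arms.

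**The case against.** A reader might infer that the article holds two opposite rules for every CNG exacerbation. It does not. The sentence on moderate events is a general severity definition that names no drug and permits no forbidden one. An exacerbation may also be mild, with no intervention, or severe, in which case quitting agrees with withdrawal. Both sections can be obeyed if the intervention is not a CNG-related medicine. The Discussion names antidepressant and anti-anxiety drugs among CNG treatments, and the forbidden-drug section lists antidepressants and sedative hypnotics as drugs to use sparingly, apart from its forbidden examples. The gap is therefore confined to a moderate exacerbation treated with a CNG-related medicine.

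Three other strong readings also fail:

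- *Withdrawal always yields a failure.* It does not; a last VAS of 0 is carried forward as a success.
- *Sites will diverge.* This is a risk, not shown. The forbidden-drug rule is explicit once such a drug is found, and investigator training, regular inspection and a blind review are planned. Training cannot, however, settle text that is itself unreconciled.
- *A definite power loss.* The article gives no exacerbation or response rate, 66 per arm is not the FAS base, and equal rates cost almost nothing.

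It can also be said that handling of rescue medication belongs in the SAP, which is not shown. That would answer a complaint about silence. Here the article itself states the endpoint definition, LOCF and evaluation at withdrawal, and together these produce the result in the first two rows of the scoring table.

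**Conclusion.** The concern stands in a limited form. Withdrawal criteria item 1, the forbidden-drug section and the adverse event section are not reconciled for a moderate CNG exacerbation treated with a CNG-related medicine. The stated scoring rules can then credit the assigned arm with pain relief obtained on that medicine, whether the patient stays in or is withdrawn at that visit.

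The bias is towards a smaller difference if such treatment is commoner on placebo. That is plausible if the drug works, but it is an assumption. Under treatment twice as common on placebo, power at 80 per arm falls from 0.91 to between 0.83 and 0.73 in the first three scenarios and to 0.59 in the most extreme. With equal 5% rates it stays at 0.907. These figures also take the planning rates, which the article calls total efficiency, as eradication rates. The point merits a change before recruitment because the correction is cheap, not because a large loss has been shown.

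**What to change.** 1. Reconcile Withdrawal criteria item 1, Concomitant treatments and forbidden drugs, and Adverse event reporting, so that one rule applies at all sites to a patient whose exacerbation is treated with a CNG-related medicine. Which clinical rule that is remains for the sponsor and investigators.
2. Add to Primary outcome: *A patient who takes any Chinese or Western medicine forbidden under Concomitant treatments and forbidden drugs before visit six is scored as not eradicated in the primary FAS analysis, whether or not the patient stays in the study. This replaces LOCF for these patients.* The rule should cover the whole forbidden category, because the drugs listed there are only examples and include no Chinese medicine.

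**Cost:** some protocol wording and one scoring line. Concomitant treatments already go in the case report form and adverse event treatments on the adverse event form, so no new data are needed. The article says the trial was still preparing to recruit. The small downside is that some patients who are pain-free on such medicine count as failures, so observed rates may be slightly lower.
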